## Abstract

*Introduction*. The etiology and pathogenesis of psoriasis are complex. Blood-heat syndrome is the core pathogenesis of psoriasis. Based on theories of Chinese medicine (CM), heat-clearing and blood-cooling (HCBC) are the primary treatment. Very few studies have investigated the pharmacological mechanism of the CM HCBC method for treating psoriasis. This multicenter randomized controlled trial will focus on treating psoriasis blood-heat syndrome with the HCBC method using Jueyin granules (JYKL). This will be an objective and standardized evaluation of the efficacy, safety, and reproducibility of the HCBC method to obtain objective evidence meeting international standards that aim to establish a clinical standard suitable for the popular application of CM for treating psoriasis. *Methods and Analysis*. A five-center randomized double-blind placebo-controlled clinical design will be used in this study. At least 196 participants will be randomly assigned to receive either JYKL or placebo treatment approximately 30 minutes after meals in the morning and evening (one sachet per time, twice daily for 8 consecutive weeks). The study duration will be 17 weeks, including 1 week of screening, 8 weeks of intervention, and 8 weeks of follow-up. The patients will be evaluated every 2 weeks, and the measures will be compared with baseline values. The primary outcome measure will be the psoriasis lesion area severity index. We will also observe the recurrence rate, body surface area, physician global assessment, dermatology life quality index, quality of life index, visual analogue scale score, CM symptom score, combined drug use, and adverse events. This trial is registered with NCT03961230.

## 1. Introduction

Psoriasis is a chronic inflammatory skin disease characterized by excessive proliferation of epidermal keratinocytes and hyperkeratosis caused by inflammatory infiltration in the dermis [1, 2]. Depending on race and region, 2–4% of the world's population suffers from psoriasis [3–5]. The prevalence of psoriasis is increasing without an increase in total cases. This may be due to increased awareness and earlier diagnosis [6]. There is currently slow recognition that psoriasis is a complex disease under a multifactor genetic model, which can be caused by the interaction of immunity, heredity, infection, and the environment [7, 8].

The etiology of psoriasis remains unclear. There are currently no fundamental drugs or treatment methods for psoriasis, which means that it is intractable and shows chronic recurrence, sometimes over an entire lifetime. Additionally, irregular or overtreatment by doctors causes tremendous financial burden and psychological stigma to patients and their families, seriously affecting quality of life [9, 10]. Therefore, a safe, effective, and economical treatment that results in a low recurrence rate is the most important goal for clinicians and researchers.

The treatment of psoriasis using modern medicine still focuses mainly on the immune system, systematic treatment, local symptomatic treatment, physical therapy, and similar methods. Most patients have achieved acceptable clinical results in the course of treatment, but side effects inevitably occur from medications, especially in systematic treatment. Therefore, a safe and effective Chinese medicine (CM) treatment has become the focus of addressing the difficulties treating psoriasis [11, 12].

The purpose of this research is to (1) enrich the scientific implication of CM in the treatment of psoriasis, (2) improve the CM methods for the clinical treatment of psoriasis, and (3) reduce the treatment cost of psoriasis.

## 2. Methods and Analysis

### 2.1. Study Design

This will be a multicenter randomized double-blind placebo-controlled clinical trial. It will aim to objectively standardize the evaluation of the clinical efficacy, safety, and recurrence of blood-heat syndrome of psoriasis vulgaris treated with HCBC in CM. The results will be helpful for establishing the clinical standard of traditional CM in the treatment of psoriasis. The trial has been registered at NCT03961230. The start and end of recruitment was planned for January 2019 and December 2021, respectively.

Prior to the commencement of the study, the investigators and researchers require uniform training to ensure that the medical staff involved in the study are fully aware of all aspects of the trial. This study will be performed in five centers in China: Yueyang Integrated Traditional Chinese and Western Medicine Hospital, Beijing Traditional Chinese Medicine Hospital, First Affiliated Hospital of Anhui University of Traditional Chinese Medicine, Affiliated Hospital of Gansu University of Traditional Chinese Medicine, and Guangxi Zhuang Autonomous Region Institute of Dermatology Prevention and Control. Competitive enrollment will be applied in all research centers to achieve the goal of 196 total participants. Each participant can be enrolled only once.

Five phases will be included in the study: screening/registration, allocation, treatment/intervention, end of the intervention, and follow-up. During the initial screening, participants will be recruited through dermatology clinics, where they will undergo a physical examination and eligibility assessment. According to the assessment results, a run-in period of up to one week will be required. All patients who are diagnosed with psoriasis with blood-heat syndrome will undergo laboratory blood testing, including a complete blood cell count, liver function test, renal function test, and a pregnancy test before study inclusion. Additionally, routine urine tests, vital sign monitoring, and physical examinations will be performed (Figure 1). Patients who are willing to join the clinical trial will receive study information and consent forms. The consent forms must be signed before a patient will be included in this study.

### 2.2. Eligibility Criteria

#### 2.2.1. Inclusion Criteria

Participants must meet all of the following criteria: (1) western medicine diagnostic criteria of drip-type or plaque psoriasis and CM syndrome diagnostic criteria of psoriasis blood-heat syndrome (this syndrome differentiation refers to the guiding principles for clinical research of new drugs of CM and the evidence-based clinical practice guide of CM for Psoriasis (2013 edition)) [26]; (2) skin lesions involving <10% body surface area (BSA) mainly located on the trunk, limbs, palms, soles, face, or scalp (vulvar area not included); (3) age 18–65 years; and (4) voluntary participation in this study and providing informed consent. There are no limitations based on sex or gender identity.

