### 2.5. Outcome Measures

#### 2.5.1. Primary Outcome

The primary outcome is the reduction in the Psoriasis Area Severity Index (PASI) score, which will be calculated as follows: PASI reduction = (PASI at baseline)–(PASI at week 8 of the treatment period).

The PASI score of the patients will be assessed every 2 weeks during the treatment period and every 4 weeks during the follow-up period. The main result of the RCT will be the percentage of patients whose PASI score decreased by more than 75% compared with the baseline at 8 weeks [2].

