#### 2.5.3. Sample Size

The sample size for this study was calculated based on the expected value of the efficacy according to the clinical trial results and data analysis of recently published articles [34, 35]. The PASI-50 reached for experimental group and control group was 55.66% and 35.3%, respectively. The significance level (alpha) was set at 0.05, and the statistical power was 80%. Based on our calculation using the PASW statistical software (V.18.0), a sample size of 89 patients was required for experimental group and control group. Given a 10% loss to follow-up, we expect to require 98 participants in each group. As a result, this trial will require at least 196 participants in its current setup.

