#### 2.5.4. Randomization, Allocation, and Blinding

This study will use central district stratification and block randomization. Random sequences will be generated by statistician researchers (implemented by the data Management Center of Jiangsu Famous Medical Technology Co. Ltd.). Eligible patients will be randomly assigned, in a 1 : 1 ratio, to one of the two groups (JYKL group or control group), aiming to balance baseline characteristics between the groups.

Throughout the study, participants, subjects, and study monitors will be blinded. Research drug random coding will be the only information linked to the group allocations. The random code will be maintained by Jiangsu Famous Medical Technology Data Management Center to ensure concealment. For the purpose of the statistical analysis, the JYKL intervention will be considered the exposure. If a serious adverse event occurs and the patient needs to be rescued, making it is necessary to know the drug used by the patient, the person in charge of each center shall decide to open the blindness and open the corresponding emergency letter. As soon as the corresponding numbered emergency letter is opened, the case will not be included in the study.

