#### 2.5.11. Statistical Analysis

The data analysis will be performed using SAS software (version 9.2). We will describe the data by using frequency counts and proportions (prevalence) for qualitative variables and means. Standard deviation (SD) will be used for normally distributed quantitative variables, while median and interquartile range (Q1 and Q3) will be used for nonnormally distributed quantitative variables. We will apply the chi-square test to examine the differences between the experimental and control groups for qualitative variables, the *t*-test to examine the differences between two groups for normally distributed quantitative variables (the homogeneity of variance will be tested between groups, and the Satterthwaite approximation will be used to correct the variance when the variance is uneven), and the Wilcoxon rank-sum test for nonnormally distributed quantitative variables. A generalized linear model will be applied for quantitative variables with repeated measures. In this study, *p* values < 0.05 (two-tailed) will be considered statistically significant.

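### Drip-type and plaque psoriasis are pooled, and form is neither a named randomisation stratum nor a factor in the stated between-arm tests; prespecifying it would be a cheap and modest gain in precision

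*Protocol article*

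**What the plan says.** **Entry.** Criterion 1 in section 2.2.1 of the protocol article is met by "western medicine diagnostic criteria of drip-type or plaque psoriasis" together with the blood-heat syndrome diagnosis. No quota or expected share is given for either form.

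**Randomisation.** Section 2.5.4 states: "This study will use central district stratification and block randomization". Patients are allocated 1:1 "to one of the two groups (JYKL group or control group), aiming to balance baseline characteristics between the groups". Centre is the only stratification factor named.

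**Outcome.** Section 2.5.1 defines the primary outcome as the PASI score at baseline minus the score at week 8, and then gives the main result as the "percentage of patients whose PASI score decreased by more than 75% compared with the baseline at 8 weeks".

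**Analysis.** Section 2.5.11 states: "We will apply the chi-square test to examine the differences between the experimental and control groups for qualitative variables". It names the t-test or the Wilcoxon rank-sum test for quantitative variables, and adds: "A generalized linear model will be applied for quantitative variables with repeated measures". The first three methods are plain two-group tests. The terms of the model are not listed. Section 2.5.10 leaves a full statistical analysis plan to a statistician; it is not available here.

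**The concern.** The article itself distinguishes two forms in its case definition and then makes no visible use of the distinction. Form is a pre-randomisation characteristic that should be established when criterion 1 is checked, and neither centre nor baseline PASI identifies it. If week-8 response differs by form whatever the treatment, a plain two-group test leaves that variation in its error term, and an uneven split of drip-type patients between the arms moves the estimated treatment difference in that trial. Because form is not a named stratum, the analysis is the remaining place to deal with it. What is at stake is some precision, in a trial whose unadjusted test has little power to spare on its own planning inputs.

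**Working it through.** **Inputs from the article.** Section 2.5.3: "The PASI-50 reached for experimental group and control group was 55.66% and 35.3%, respectively"; alpha 0.05; power 80%; 89 per group; 98 per group after 10% loss. Section 2.5.11: two-sided testing.

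**The plan's own figure.** With unpooled variance, n = (1.96 + 0.8416)² × [p1(1−p1) + p2(1−p2)] / (p1−p2)².
- p1(1−p1) = 0.5566 × 0.4434 = 0.2468, and p2(1−p2) = 0.353 × 0.647 = 0.2284, sum 0.4752.
- (0.5566 − 0.353)² = 0.2036² = 0.04145.
- n = 7.849 × 0.4752 / 0.04145 = 89.97. This is 89 if truncated, and 89 × 1.10 = 97.9 gives 98. The stated sizes are reproduced to within one patient per arm.
- The ordinary chi-square test, which uses the pooled variance, has power 78.4% at 89 per arm.

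**Assumptions, not in the article.** Let q be the drip-type share and D the difference in week-8 response between forms, taken as equal in both arms. Neither is given. The ranges examined are q = 10% to 50% and D = 10 to 40 points.

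**Chance imbalance.** The SD of the between-arm difference in drip-type share is √(2q(1−q)/89): 4.5 points at q = 10%, 6.0 at 20%, 6.9 at 30% and 7.5 at 50%. Its expected value is zero. An imbalance above 10 points occurs in 2.6% of trials at q = 10% and 18.2% at q = 50%. The 95% limit of the resulting shift in the risk difference is 1.96 × SD × D. For q = 30% and D = 30 points this is 1.96 × 0.0687 × 0.30 = 0.040, or 4.0 points against the planned 20.4.

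**Variance removed by stratifying.** This is 2q(1−q)D² / [p1(1−p1) + p2(1−p2)]. For q = 30% and D = 30 points it is 2 × 0.3 × 0.7 × 0.09 / 0.4752 = 0.0378 / 0.4752 = 8.0%, equivalent to about 14 of the 178 evaluable patients.

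**Power.** A simulation with 89 per arm and 100,000 trials per scenario held the overall rates at 55.66% and 35.3%. Form-specific rates were p − qD for plaque and p + (1−q)D for drip-type. The plain chi-square test was compared with a Cochran-Mantel-Haenszel (CMH) test stratified by form.

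| q | D (points) | 95% limit of shift (points) | Variance removed | Patients of 178 | Power, chi-square | Power, CMH |
|---|---|---|---|---|---|---|
| 10% | 10 | 0.9 | 0.4% | 0.7 | 78.3% | 78.2% |
| 20% | 20 | 2.4 | 2.7% | 4.8 | 78.2% | 79.3% |
| 30% | 20 | 2.7 | 3.5% | 6.3 | 78.3% | 79.5% |
| 30% | 30 | 4.0 | 8.0% | 14.2 | 78.0% | 81.3% |
| 50% | 40 | 5.9 | 16.8% | 30.0 | 78.4% | 85.3% |

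**Type I error.** With both arms at 35.3%, the plain chi-square test rejected in 4.9% to 5.2% of trials in every scenario.

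**Limit of the calculation.** The rates are for PASI-50, whereas section 2.5.1 uses a fall above 75% and an absolute PASI reduction. The article gives no planning rates for the former and no standard deviation for the latter, so the figures only illustrate the effect on the article's own inputs.

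**The case against.** The strongest reply is that covariates and strata belong in the analysis plan, which is not shown, and that the one thing the article fixes firmly, randomisation by centre, would not change. This stands in part. Silence on covariates would be weak evidence by itself, and the repeated-measures model leaves its terms open. But section 2.5.11 does not merely omit detail: it names plain two-group tests, and a test stratified by form is a specific alternative to them.

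Second, the article does not say that the forms differ in course or response. This stands, and it is why the gain can be given only as a range that starts at zero. A reader might infer that drip-type disease settles without treatment within the 8 weeks, so that the result would partly reflect natural remission. The article says nothing of the kind.

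Third, pooling is the stated design: the target is psoriasis vulgaris with blood-heat syndrome, and no objective asks for effects by form. This also stands. With a drip-type share of 10% to 30%, 89 per arm gives about 9 to 27 drip-type patients per arm, too few for useful treatment effects by form.

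Fourth, no passage lists form as a recorded variable. Criterion 1 cannot be confirmed without a diagnosis, and Table 2 schedules a clinicopathological evaluation and medical history at screening, so the information should exist. It would still have to be captured as a data item.

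None of this shows a material harm from one prespecified two-level baseline factor.

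**Conclusion.** The point holds as a suggestion for better precision. Two forms are pooled, form is not a named stratum, and the stated between-arm tests do not use it. The gain in power from using it runs from none to about 7 points over the ranges examined, and is about 1 point at a 20-point response gap. Gains of 3 points or more need a gap of 30 points or more and a drip-type share that is not small. These figures rest on an assumed share, an assumed gap that is equal in both arms, and PASI-50 rates standing in for the article's own endpoints.

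A reader might infer that leaving form out biases the week-8 result. It does not: randomisation makes the expected imbalance zero, the unadjusted test keeps its 5% level, and the chance variation is already in its standard error. A shift of several points describes an unlucky single trial under the larger assumed gaps, not a systematic error. Nor do the documents show that the randomisation scheme is defective or that the pooled estimate is uninterpretable.

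**What to change.** Before unblinding, make these additions to the analysis plan:
- Use psoriasis form (drip-type or plaque) as a stratum in the week-8 responder comparison, for example a Cochran-Mantel-Haenszel test in place of the plain chi-square test.
- Include form as a fixed factor, alongside treatment, in the model for PASI reduction.
- Report response and recurrence by form descriptively, without formal by-form claims.

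Leave randomisation unchanged. Adding form to it would give 5 × 2 = 10 strata across five competitively enrolling centres, and adjusting in the analysis is simpler.

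The cost is a line or two of analysis wording and making sure that form is captured as a baseline item for every patient. No patients or visits are added. The drawback is that the gain is negligible if the forms respond alike or drip-type patients are rare.

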#### 2.2.2. Exclusion Criteria

Participants with be excluded if they meet any of these exclusion criteria: (1) presence of other active skin diseases that may affect the study; (2) history of systematic treatment with research drugs, biological agents, or immunosuppressants within the past 30 days; (3) history of receiving topical glucocorticoid, phototherapy, or similar treatment within the previous 14 days; (4) currently experiencing a severe and uncontrollable period of local or systemic acute or chronic infection; (5) presence of serious systemic diseases or the clinical detection indexes belonging to one of the following conditions—increase in glutamic pyruvic transaminase or glutamic oxaloacetic transaminase is more than 1.5 times of the upper limit of the normal value, an increase in creatinine, and any of the leading indicators of blood health (white blood cell count, red blood cell count, hemoglobin count, and platelet count) outside the normal range or other laboratory abnormalities as judged by researchers to be unsuitable for patients participating in this trial; (6) history of malignant tumors and patients with primary or secondary immunodeficiency and hypersensitivity; (7) major surgery within the previous 8 weeks or will be required during the study period; (8) currently pregnant or lactating; (9) history of alcoholism or drug abuse; (10) history (or family history) of severe mental illness; or (11) a family history of cancer.

### 2.3. Interventions

#### 2.3.1. Experimental Group: JYKL and Basic Treatment

The JYKL to be used in this study is produced and supplied by Hefei Sanjiu Pharmaceutical Co. Ltd.

Dosage and usage: JYKL will be administered approximately 30 minutes after meals in the morning and evening (one sachet per time, two times daily for consecutive 8 weeks). The specific administration method will be as follows: empty the content of one sachet into a mug, add 50 mL of warm water, stir until dissolved, and add another 50 mL of hot water. Consume all 100 mL of the liquid mixture as a single dosage. The participant will be asked to wear warm clothes.

#### 2.3.2. Control Group: Placebo and Basic Treatment

The placebo to be used in this study is also produced and supplied by Hefei Sanjiu Pharmaceutical Co. Ltd.

Dosage and usage: the placebo will be dosed and administered in the same manner as the JYKL.

Basic treatment is administered as follows:Moisturizing: as a basic treatment, the use of a moisturizer is always necessary. Moisturizing and moisturizing agents will be applied to areas of the skin that do not erode late at night, including dry nonrash areas. A soft moisturizer without spices will be used; for sensitive and dry skin, a Yuze moisturizer is recommended.Bathing and cleansing the skin: a reasonable bath which involves a quick overall rinse with warm water (35°C–39°C) for about 5 minutes once a day is indicated. The participant should then immediately apply moisturizing agents within 2 minutes after bathing to avoid skin dehydration. The use of alkaline detergents should be avoided.Avoid aggravating factors: patients with food allergies should avoid eating allergy-aggravating foods to prevent inducing a psoriasis reaction.Reasonable lifestyle: avoid staying up late, minimize stress, avoid spicy and irritating foods, stay physically active, and maintain regular bowel movements.Adhere to reasonable treatment: doctors and patients should communicate regularly and establish mutual trust. Adhere to the treatment regimen for the best chance of alleviating the disease.

### 2.4. Combined Use of Drugs

Permissible combined treatment: participants may take drugs for other diseases (such as hypertension, diabetes, acute infection, or other reasons) if other drugs have not been confirmed as effective for treating psoriasis.Prohibition of combined treatment: drugs that may induce or aggravate psoriasis may not be taken during the study.

### 2.5. Outcome Measures

#### 2.5.1. Primary Outcome

The primary outcome is the reduction in the Psoriasis Area Severity Index (PASI) score, which will be calculated as follows: PASI reduction = (PASI at baseline)–(PASI at week 8 of the treatment period).

The PASI score of the patients will be assessed every 2 weeks during the treatment period and every 4 weeks during the follow-up period. The main result of the RCT will be the percentage of patients whose PASI score decreased by more than 75% compared with the baseline at 8 weeks [2].

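### Section 2.5.1 gives two incompatible primary endpoints (absolute PASI reduction and PASI-75 response at week 8), and the stated power belongs to neither

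*Protocol article*

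**What the plan says.** Section 2.5.1 opens with "The primary outcome is the reduction in the Psoriasis Area Severity Index (PASI) score" and gives the formula "PASI reduction = (PASI at baseline)–(PASI at week 8 of the treatment period". This is an absolute difference in PASI points. The same section ends: "The main result of the RCT will be the percentage of patients whose PASI score decreased by more than 75% compared with the baseline", with week 8 as the time point. This is a yes/no response relative to each patient's own baseline (PASI-75).

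The other places that could settle the matter do not:

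- **Abstract:** "The primary outcome measure will be the psoriasis lesion area severity index". It names the instrument but not the measure taken from it.
- **Section 2.5.2, secondary parameters:** neither PASI-75 nor PASI reduction is listed, so neither is demoted.
- **Section 2.5.3, sample size:** the planning rates are for another cut-off: "The PASI-50 reached for experimental group and control group was 55.66% and 35.3%, respectively".
- **Section 2.5.11, statistical analysis:** tests are assigned by type of variable, followed by one general threshold: "values < 0.05 (two-tailed) will be considered statistically significant".

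**The concern.** A confirmatory trial needs one answer to the question of what result would count as success. Here the section that should give it gives two. The choice matters because the measures are different quantities. A patient with baseline PASI *B* has a PASI-75 response only if the reduction exceeds 0.75 × *B*, so the same fall in points can be a response in a mild case and a non-response in a more severe one. The mean absolute reduction is driven by patients with high baseline scores, whereas PASI-75 counts every patient equally. A treatment effect can therefore show on one and not on the other.

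Two things are at stake. The first is the interpretation of a split result: the protocol gives no basis for calling it positive or negative. The second is that a choice of primary made after the data are seen would not hold the 5% error rate. In addition, the stated 80% power describes neither of the two measures.

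**Working it through.** **1. The two definitions side by side**

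| | Definition A | Definition B |
|---|---|---|
| Label in 2.5.1 | primary outcome | main result of the trial |
| Quantity | PASI at baseline minus PASI at week 8 | PASI fall of more than 75% from baseline at week 8 |
| Type | continuous, absolute | binary, relative |
| Test under 2.5.11 | t-test or Wilcoxon rank-sum; or the generalized linear model for repeated measures, since PASI is scored every 2 weeks | chi-square |

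A does not contain B: to get from A to B one must divide by baseline and apply a cut-off, and the section makes no such link.

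**2. The plan's own sample size**

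Inputs from 2.5.3 and 2.5.11: p1 = 0.5566, p2 = 0.353, two-sided alpha 0.05, power 80%; 1:1 allocation from 2.5.4. With the unpooled variance formula:

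n = [p1(1 − p1) + p2(1 − p2)] × (1.960 + 0.842)² / (p1 − p2)²

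= (0.2468 + 0.2284) × 7.849 / 0.04145 = 89.97 per arm.

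This agrees with the stated 89 (truncated). Adding 10% gives 89 × 1.10 = 97.9, hence 98 per arm and 196 in total. The arithmetic reproduces, but for PASI-50, which is neither A nor B.

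**3. What 89 per arm means for the candidates**

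For A, the article gives no target difference and no standard deviation, so its power cannot be computed. For B, it gives no PASI-75 rates. As an illustration only, assume that the odds ratio implied by the PASI-50 rates carries over: (0.5566/0.4434) / (0.353/0.647) = 1.255/0.5456 = 2.30. Power is from the two-proportion test with pooled variance under the null, two-sided 0.05, 89 per arm:

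| Assumed control PASI-75 | Implied JYKL PASI-75 | Power |
|---|---|---|
| 5% | 10.8% | 30% |
| 10% | 20.4% | 49% |
| 15% | 28.9% | 61% |
| 20% | 36.5% | 69% |

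A larger effect on PASI-75 would give more. With a 20-point difference over a 10% control rate, for example, power is 92%. The table shows that the 80% cannot be carried over without its own assumptions. It does not show that the trial is underpowered.

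**4. Error rate if either result could be claimed**

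This is conditional on a rule that the protocol does not state. With two test statistics Z1 and Z2, bivariate normal under the null with correlation r, the chance of at least one false positive is 1 − P(|Z1| ≤ 1.96 and |Z2| ≤ 1.96):

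| Assumed r | False-positive rate |
|---|---|
| 0.3 | 9.5% |
| 0.5 | 9.1% |
| 0.7 | 8.3% |
| 0.9 | 7.0% |

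Independence would give 1 − 0.95² = 9.75%, which is too high here because both measures come from the same PASI scores. As a check on plausible r, PASI-like data were simulated with no treatment effect: 89 per arm, lognormal baseline, and null PASI-75 rates of about 9% to 23%, all assumed. The correlations were 0.41 to 0.58 and the either-test error 8.6% to 9.2%, inside the range above.

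**The case against.** **A single-primary reading exists.** One can take PASI as the outcome, as the abstract does, and PASI-75 as the way in which the result will be reported. The defect would then be loose wording. But section 2.5.1 attaches the word primary to an absolute difference with its own formula, and a responder rate is not a summary of that difference. The reading is possible; the text does not establish it.

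**The analysis plan may deal with multiplicity.** Section 2.5.10 says that a statistician will write one, and test ordering or division of alpha is commonly left there. That stands: their absence from this article is not the point. Which measure is primary is for the protocol to say, and the protocol says it twice, differently.

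**The protocol never says that either test suffices.** This also stands. A reader might infer from the two definitions and the general 0.05 threshold that the trial has been given two chances to succeed. Section 2.5.11 only states a threshold for significance; it does not assign 0.05 to each of two primary tests or say that one positive result is enough. The 7% to 9.5% is what would follow under such a rule, not a property of the plan as written.

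**PASI-50 is not a third test.** A reader might add it and arrive at a higher error rate. It appears only as a planning rate in section 2.5.3 and is listed nowhere as an outcome to be tested, so no three-endpoint error rate is warranted.

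**Conclusion.** The contradiction is stated in the protocol itself and should be resolved before unblinding. Section 2.5.1 defines the primary endpoint in two incompatible ways, no other section ranks them, and the 80% power with 89 per arm applies to PASI-50 alone.

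The main consequence needs no assumption: if the two week-8 results differ, the plan cannot say whether the trial succeeded. The error rate of about 7% to 9.5% rests on two assumptions, namely that either result could be claimed and that the tests correlate between 0.9 and 0.3. The power figures for PASI-75 rest on assumed control rates and a carried-over odds ratio. They illustrate that power depends on the choice of endpoint, and they do not support a claim that the sample size was miscalculated or is too small.

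**What to change.** Before unblinding, amend section 2.5.1, and the registry entry with it, to name one of the two week-8 measures as the sole primary endpoint at two-sided 0.05. Make the other a secondary endpoint, tested only if the primary is significant. Which of the two to name is the sponsor's choice; the article gives grounds for either. PASI-50 need not be added to the testing sequence.

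Restate section 2.5.3 for the named primary at the planned 89 evaluable per arm, with the assumptions given: expected rates if PASI-75 is chosen, or a target difference and standard deviation if PASI reduction is chosen. The PASI-50 figure should not be carried over.

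The cost is a protocol amendment, a registry update and one recalculation. No new visits or measurements are needed, because PASI is already scored at baseline and week 8. There are two downsides: the demoted measure can no longer carry a positive claim alone, and the restated power may be below 80%, which the sponsor would then have to accept or address. Once the data are unblinded, the choice can no longer be made credibly.
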